## Abstract

**Introduction:**

Diarrhoeal disease remains a leading cause of mortality and morbidity worldwide. Cholera alone is estimated to cause 95,000 deaths per year, most of which occur in endemic settings with inadequate water access. Whilst a global strategy to eliminate cholera by 2030 calls for investment in improved drinking water services, there is limited rigorous evidence for the impact of improved water supply on endemic cholera transmission in low-income urban settings. Our protocol is designed to deliver a pragmatic health impact evaluation of a large-scale water supply intervention in Uvira (Democratic Republic of the Congo), a cholera transmission hotspot.

**Methods/design:**

A stepped-wedge cluster randomised trial (SW-CRT) was designed to evaluate the impact of a large-scale drinking water supply intervention on cholera incidence among the 280,000 inhabitants of Uvira. The city was divided into 16 clusters, where new community and household taps will be installed following a randomised sequence over a transition period of up to 8 weeks in each cluster. The primary trial outcomes are the monthly incidence of “confirmed” cholera cases (patients testing positive by rapid detection kit) and of “suspected” cholera cases (patients admitted to the cholera treatment centre). Concurrent process and economic evaluations will provide further information on the context, costs, and efficiency of the intervention.

**Discussion:**

In this protocol, we describe a pragmatic approach to conducting rigorous research to assess the impacts of a complex water supply intervention on severe diarrhoeal disease and cholera in an unstable, low-resource setting representative of cholera-affected areas. In particular, we discuss a series of pre-identified risks and linked mitigation strategies as well as the value of combining different data collection methods and preparation of multiple analysis scenarios to account for possible deviations from the protocol. The study described here has the potential to provide robust evidence to support more effective cholera control in challenging, high-burden settings.

**Trial registration:**

This trial is registered on clinicaltrials.gov (NCT02928341, 10th October 2016) and has received ethics approval from the London School of Hygiene and Tropical Medicine (8913, 10603) and from the Ethics Committee from the School of Public Health, University of Kinshasa, Democratic Republic of the Congo (ESP/CE/088/2015).

## Introduction

Despite substantial progress in recent decades, diarrhoeal disease remains a leading cause of mortality and morbidity worldwide [1, 2]. In 2015, an estimated 2.3 billion cases of diarrhoea occurred globally, including almost one billion cases in children under five, causing half a million deaths, mostly in sub-Saharan Africa and South Asia [1]. Early childhood diarrhoea may have long-term consequences including stunting and impaired cognitive development [3, 4]. A broad range of enteric pathogens can cause diarrhoeal disease, including Rotavirus, *Cryptosporidium* spp., *Shigella* spp., and enterotoxigenic *E. coli* (ETEC), with aetiology varying by age and setting [1, 5].

The diarrhoeal disease cholera is caused by toxigenic *Vibrio cholerae* O1 or O139 and is characterised by acute watery diarrhoea. Cholera remains an important cause of diarrhoeal disease morbidity and mortality, with an estimated 1.3 to 4 million cases and 95,000 deaths globally in 2015 [6]. Approximately half of cholera deaths occur in children under five [7], and the cholera burden is concentrated in endemic settings in Asia and Africa [6]. In recent years, large outbreaks in Haiti [8] and in Yemen [9] have highlighted the vulnerability to cholera of populations affected by humanitarian crises [10–13]. In sub-Saharan Africa, identified transmission “hotspots” which represent less than 4% of the region’s total population account for over half of the total cholera morbidity burden [14].

In response to the ongoing challenge of cholera prevention and control, the World Health Organization (WHO)-led Global Task Force on Cholera Control (GTFCC) has set an international goal of reducing cholera deaths by 90% by 2030 [15]. In order to achieve this ambitious target, the GTFCC promotes a multisectoral approach targeting transmission hotspots via three axes [15]: (a) surveillance and health systems strengthening; (b) vaccination campaigns; and (c) long-term improvements in water, sanitation, and hygiene (WASH) services.

The first axis of surveillance and monitoring of cholera is often hindered by weak national health systems in those countries where cholera is endemic [6, 16–18], and there is substantial underreporting [6]. Another challenge lies in the broad criteria of the WHO’s cholera case definition [19] which defines a “suspected cholera case” in endemic areas as presentation of acute watery diarrhoea with or without vomiting. These broad clinical criteria can lead to misdiagnosis of cholera cases, and whilst WHO recommends laboratory confirmation, suspected cases are not consistently confirmed by laboratory methods [18]. Studies from several African countries [20–22] and from Haiti [23, 24] found laboratory confirmation by culture of between 0 and 63% of suspected cholera cases.

The second axis, vaccination campaigns, is supported by oral cholera vaccines (OCV) which can provide protection against cholera for 2 to 4 years [25, 26] and indirect protection via herd immunity has also been documented [27–30]. A global stockpile was created in 2013 to ensure OCV availability for cholera control in outbreaks and humanitarian emergencies [31]. As OCV supply capacity increased in recent years, mass vaccination campaigns in transmission hotspots, in conjunction with improvements in WASH services, are now the foundation of the GTFCC strategy to eliminate cholera along with effective surveillance [15].

The third axis is long-term improvements in WASH services for cholera prevention, which aligns with Sustainable Development Goal (SDG) 6: universal access to safely managed water and sanitation services by 2030 [32]. Diarrhoeal diseases such as cholera are generally transmitted faecal-orally via environmental routes such as contaminated water or food [33]. WASH interventions can interrupt this environmental transmission and substantially reduce diarrhoeal disease risk [34]. However, 785 million people still did not have access to basic drinking water services in 2017 [35] and in a recent analysis, 60% of the diarrhoeal disease global morbidity burden was attributable to inadequate WASH services [36]. Improving the microbial quality of drinking water can prevent waterborne (and foodborne, where water is used in food preparation) transmission of diarrhoeal diseases whilst improving the supply or quantity of water available can prevent water-washed transmission of diarrhoeal diseases through enabling better personal and domestic hygiene. The latter may be key to cholera control, as recent studies have highlighted the importance of cholera transmission within households during outbreaks [37–41].

Whilst the link between drinking water access and risk of diarrhoeal disease and cholera is well established, there is limited evidence in the scientific literature on the impacts of large-scale improvements in water supply or sanitation infrastructure intended to reduce the burden of diarrhoeal diseases and cholera [34, 42]. This research gap is likely due to methodological as well as logistical and financial challenges related to conducting rigorous evaluations of technically complex, long-term interventions. Research challenges are enhanced in the complex, resource-limited, and often unstable contexts where the cholera burden is concentrated [13, 43] and the health impacts of WASH interventions are under-researched in humanitarian settings [44].

Since 2012, the Agence Française de Développement (AFD) and the Veolia Foundation (VF), with support from the European Union, have invested approximately 13 million euros in improvements to the water supply infrastructure in Uvira (Democratic Republic of the Congo, DRC), an identified hotspot for cholera transmission [14]. They commissioned an independent evaluation of the health impact of the planned works. This project offered a rare opportunity to investigate how improvements in urban water supply infrastructure, in a conflict-affected, cholera-endemic area, influence the incidence of cholera and other diarrhoeal diseases. In light of the potential public health value of such research but with consideration of the multiple challenges for implementation in this setting, we employed a deliberately pragmatic approach to this study protocol. The aim of this study is to evaluate the impacts of water supply infrastructure improvements on cholera and other diarrhoeal diseases in Uvira (DRC). We have identified a number of potential risks to the study and then pre-specified mitigative measures that would permit the assessment of health impact under different scenarios. This protocol and analysis plan are shared here in accordance with best practice principle for pre-specification but also to stimulate debate in the global health sector on strategies for undertaking rigorous research in unstable settings.

## Methods—trial design

Our study combines an open-cohort, stepped-wedge, cluster randomised trial (SW-CRT) and interrupted time series (ITS) analysis, with cross-sectional surveys of water-related practices, an economic and a process evaluation. Our approach is deliberately pragmatic with the different study components designed to mitigate a range of pre-identified risks to this study which relate to the delivery of a complex intervention in a challenging context.

Methods are described in accordance with the SPIRIT guidance [45] and the Consolidated Standards of Reporting Trials (CONSORT) extension for SW-CRT [46] to ensure adequate inclusion and reporting of key design and analysis components during development of this protocol. The SPIRIT check-list is available in Additional file 1.

### Aim and objectives

The aim of this study is to evaluate the impact of improved water services on cholera and other diarrhoeal diseases in the town of Uvira (DRC). The primary objective is to assess changes in the monthly incidence of suspected and confirmed cholera cases admitted to the main cholera treatment centre (CTC) in Uvira (using SW-CRT and ITS analyses). Additional objectives are to assess (1) changes in domestic water-related practices (using cross-sectional surveys, and REGIDESO operational and billing information); (2) cost-effectiveness and cost-benefit of water supply improvements (through an economic evaluation); and (3) fidelity and compliance of the planned water supply intervention (through a process evaluation). Each of these study components is described below, followed by the analysis plan, household surveys, and economic and process evaluations.

### Study setting

Uvira is a town of approximately 280,000 inhabitants on the shore of Lake Tanganyika, in Eastern DRC (South Kivu) [47]. The region is characterised by protracted conflict and ethnic violence [48], with at least 100 active armed groups identified in South and North Kivu as of 2019 [49] and continuing, massive population displacements [50].

Cholera has been endemic in the region since the 1970s and Uvira is located within an internationally designated transmission “hotspot” [14, 51]. The CTC located in the General Hospital in Uvira is the main care structure for acute diarrhoea cases—defined as three or more loose or watery stool per day—for the city and provides free treatment including rehydration and, in some cases, antibiotics [21]. CTC admissions have been recorded by the study team since 2009, with an average of 1266 patients admitted annually or 3.4 admissions per year per 1000 inhabitants.

The WHO/UNICEF Joint Monitoring Program estimates that in 2017 approximately 36% of households in DRC relied on unimproved drinking water services and an additional 9% used surface water as their primary source [35]. The existing water supply infrastructure in Uvira was established in the colonial era (1958) [52] and was severely damaged during the First Congo War (1996–1997), with parts then repaired and/or modified by NGOs in the early 2000s. In 2018, before the planned intervention began, the water supply system in Uvira provided a partial and intermittent piped water service that reached an estimated 31% of the population [52]. Surveys conducted by the study team in preparation for the trial in 2016 and 2017 indicated that almost half (47%) of the participants (747 respondents from 458 households) reportedly used surface water—lake (13%) or rivers (34%), about a third (34%) used a tap outside their compound, and 18% had a tap in their compound as primary drinking water source (unpublished data).

### Rationale for using a cluster design and rationale for using a stepped-wedge design

A SW-CRT design was selected due to the nature and scale of the intervention, which involves the rehabilitation of structural water supply network components as well as the extension of that network. A cluster randomised design was selected because infrastructure improvements (e.g. piped network rehabilitation and extension or installation of community taps) will affect large numbers of water service users simultaneously. The stepped-wedge design overcomes the logistical constraint of not being able to deliver the intervention concurrently to all clusters due to the duration of the construction works. It also addresses ethical concerns by allowing water supply improvements to be delivered to the entire town of Uvira without causing delays. SW-CRT designs have been used previously for the evaluation of large-scale water treatment, supply, and/or management interventions in India [53], Bangladesh [54], and Mexico [55] but never for systems which include new household and community water connections, and never in a cholera-endemic setting.

### Intervention

The water supply intervention consists of a package of infrastructure works designed to improve the piped water service in Uvira (Fig. 3).

First, core components of the water supply network will be targeted and these works are expected to affect all clusters. The water treatment plant will be retrofitted with a system including flocculation, settling, sand filtration, and chlorination, and new pumps will be installed to double the water treatment plant production capacity. A new tank (2000 m^3^) will be built, increasing the available hydraulic head for water distribution and doubling the overall storage capacity for the town. Structural pipes (diameter ≥ 250 mm) will be installed and those with identified deficiencies will be rehabilitated (7.4 km total).

Second, at the cluster level, the secondary network will be extended to increase coverage and create loops, which are expected to improve the reliability of water distribution locally. The installation of 116 (expected range 100–120) new community taps is planned within the project, along with works on 3000 household connections, including approximately 1000 new taps for households that are currently not connected to the water supply network. While the total number of household connections (new and rehabilitated) included in the project is set to 3000, the total number of new household connections and the distribution of these connections between clusters will remain flexible for the reasons described in more detail below. Household-level connections and community taps will be installed in each cluster following the randomised allocation sequence (Table 1).

The Uvira water network is, and will continue to be, managed by the national company Régie de Distribution d’Eau de la République Démocratique du Congo (REGIDESO). Three committees will be formed by community members for the management of community taps with the support of a Congolese NGO that has led successful community engagement projects (ADIR). These committees will be responsible for the daily management of water distribution at the community taps and the collection of water consumption fees from users to pay monthly bills sent by REGIDESO to each committee.

REGIDESO will be responsible for the promotion of new household connections in each neighbourhood/cluster via appropriate communication channels. New household connections will be installed on a “first come, first served” basis in each cluster after interested individuals submit an application form to REGIDESO and pay a fee, partially subsidised by the project. The number of new household connections planned in each cluster is based on three parameters as part of the works planning (Table 1): the number of connections per 1000 inhabitants in each cluster, the proportion of the population with access to a tap within 300 m, and the network capacity in terms of number of total expected connections per meter of pipe within the cluster. However, given the reliance on individual demand for the installation of new household connections, and potential variability thereof, the team supervising construction works will be given discretion to reallocate new household connections to different clusters. Alternatively, in an attempt to facilitate the roll-out of the intervention, they may increase the proportion of household connections to rehabilitate according to identified needs and demands.

The management structure for the construction works is as follows: VF is leading the supervision of the works, including adhesion to the study protocol, with regular visits to the construction site and has contracted an engineering consulting firm for daily follow-up activities. The construction company was hired by REGIDESO, with AFD and VF support, after an international call for tender and is bound by a contract that specifically requires works to be implemented following the cluster randomisation protocol for the SW-CRT described below.

### Description and diagram of trial design

The town of Uvira was divided into sixteen clusters stratified into two groups due to the project funding structure and planned works sequence: South (*n* = 6, areas primarily served by the existing tank) and North (*n* = 10, areas primarily served by the new tank) (Fig. 1). The existing and new tank will both eventually belong to the same water supply network and contribute to improving water service across all clusters. The primary criteria used to define clusters were the total length of pipes to be rehabilitated or installed and the number of new community taps; the secondary criteria included considerations such as alignment with existing administrative zones and natural features such as rivers. Key characteristics of the study clusters are presented in Table 1.

**Fig. 1 Fig1:**
[figure not shown]
Map of Uvira with the definition of clusters and groups: South (blue, *n* = 6) and North (pink, *n* = 10)

**Table 1 Tab1:** Key cluster characteristics

Cluster #	Estimated population (March 2018)	Area [km^2^]	*Mean # suspected cholera cases per month	*Mean monthly incidence per 1000	Existing pipe length [m]	Pipe length to rehabilitate [m]	Length of new pipes to install [m]	# existing household connections	# provisionally planned new household connections	Number of planned new community taps	Allocation sequence
1	4291	2.02	1.9	0.4	2152	57	2628	16	66	6	15
2	4990	0.76	6.0	1.2	1578	1658	1792	89	25	3	16
3	11,183	0.87	6.4	0.6	5574	1266	1864	171	25	7	10
4	7328	1.02	5.4	0.7	2347	0	3398	25	100	5	12
5	13,649	1.27	4.4	0.3	2786	797	4177	19	205	4	9
6	8389	0.48	5.8	0.7	1730	499	2328	43	82	6	13
7	7480	0.37	2.0	0.3	4525	367	1065	152	26	2	8
8	15,455	0.43	4.8	0.3	2961	1097	1793	199	25	5	7
9	3994	0.36	9.4	2.4	3848	189	2446	183	25	8	11
10	14,175	0.59	7.1	0.5	8901	692	1520	525	25	7	1
11	56,106	1.70	14.5	0.3	8775	1599	2401	633	254	16	5
12	12,462	0.99	3.0	0.2	2292	1455	1844	22	193	1	14
13	50,764	2.75	10.4	0.2	17,781	1666	1266	1384	24	11	4
14	16,175	0.55	6.7	0.4	907	0	2549	35	220	5	3
15	15,183	0.81	7.2	0.4	4091	135	2420	161	62	9	2
16	19,338	1.98	10.6	0.6	1788	2061	2874	28	318	20	6
**Mean**	**16,310**	1.06	6.6	0.4**	72,033	13,538	36,363	3685	1675	7.2	–
Minimum	3994	0.36	1.9	0.2	907	0	1065	16	25	1	–
Maximum	56,106	2.75	14.5	2.4	17,781	2061	4177	1384	318	20	–

*Based on CTC admissions between January 1, 2009, and March 31, 2018, and population in March 2018

**Mean weighted by cluster population size

Within each group (South and North), clusters were randomised to different initiation periods by the research team using a random number generator, with the intervention delivered to the South clusters first. The intervention interval—or “step”—during which time a given cluster receives the intervention was planned to be 4 weeks; this interval was extended to up to 8 weeks for the installation of new household connections to the water supply network (Fig. 2)—the reasons are discussed below.

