### Analysis plan

The SW-CRT and ITS analyses are detailed hereafter.

A generalised estimating equations (GEE) Poisson regression for rates will be used with robust standard errors. An indicator of water service quality will be included, which may integrate users’ distance to taps, hours of water availability, or volumes distributed, for example, to reflect improvements brought by the intervention in terms of water service. To account for seasonality a harmonic term for time (in months) will be included. This analysis accounts for correlations between individuals within clusters, as well as repeated measures of the same clusters over time. A small sample correction will be considered to adjust for the small number of clusters [57]. Note that data collected during the transition period for each cluster will not contribute to the analysis.

Since the intervention takes place over less than 2 years, the seasonal pattern of cholera infection may not be estimated correctly using only data from the trial period. A sensitivity analysis will be carried out using historical data from the cholera treatment centre which is available from 2009 to the start of the trial. The model will be re-fitted using the same covariates, with all historical data considered non-intervention time. We will also consider the inclusion of a treatment by time interaction term in the GEE model as part of further sensitivity analyses linked to seasonality.

An intention-to-treat analysis will be carried out for the main analysis. The above models will be repeated with the other primary outcome: rate of confirmed cholera cases per 1000 residents.

Randomisation may be particularly challenging to ensure given the nature of the intervention. If the randomisation scheme is not adhered to, balance between arms cannot be assumed. In this case, relevant confounders which may be associated with intervention allocation and outcome will be included in the main analysis, as they would be in non-randomised settings. These may include patient’s age and sex, and factors related to their household location such as water service quality and distance from the cholera treatment centre.

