### Research-specific challenges and limitations

From a research standpoint, the fact that the new tank, which is expected to improve service quality in all clusters, will be put into service half-way through cluster-level improvements (Fig. 2) and the flexible step duration (and o verlap between steps) to allow prolonged installation of new household connections—another pragmatic choice required to adapt to the context—both represent deviations from a standard SW-CRT roll-out. Likewise, the heterogeneity in cluster characteristics (Table 1), due to local constraints, is large for a SW-CRT. These aspects will be accounted for in the stepped-wedge analysis by considering potential confounders. An ITS analysis will also be conducted, which does not depend in any way on the intervention structure and implementation.

Spill-over effects could also potentially undermine the study design if inhabitants of a control cluster are able to use an improved “intervention” water service in a neighbouring cluster; for example, if a new private connection is used by multiple households. While household surveys may provide insights into the actual use of water services, we will not be able to systematically assess intervention compliance over the entire city. An intention-to-treat approach will therefore be used in the analysis and a sensitivity analysis will be performed to assess the influence of excluding participants who live within spatial buffers of different widths along the clusters’ borders. Given the predominance of within-household cholera transmission over infection from environmental sources [41, 61], we expect spill-over effects, if any, to remain of limited magnitude.

The reliance on clinical surveillance to assess cholera incidence is another limitation of this evaluation, as it may be influenced by healthcare-seeking behaviour. Although we will not be able to quantify CTC attendance rates for diarrhoeal disease symptoms across Uvira, we will seek to collect information on care habits during the household survey and critically review assumptions related to healthcare use for diarrhoeal diseases. The confirmation of cholera cases by RDTs rather than by culture or molecular methods (PCR) also responds to the need for pragmatic research approaches, as RDTs were identified as the only confirmation method that could be reliably used in the Uvira context considering available resources and laboratory capacity at the time this study started.

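### Clusters were randomised only within South and within North, but the primary model has one town-wide time term, so part of the effect estimate is a non-randomised South-versus-North contrast

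*Protocol article*

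**What the plan says.** The Description and diagram of trial design section describes "sixteen clusters stratified into two groups due to the project funding structure and planned works sequence": South with 6 clusters and North with 10, the latter being "areas primarily served by the new tank". Below Table 1 it adds: "Within each group (South and North), clusters were randomised to different initiation periods by the research team using a random number generator". The order of the two groups themselves was fixed rather than drawn, "with the intervention delivered to the South clusters first". The step "was planned to be 4 weeks; this interval was extended to up to 8 weeks" for household connections.

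The Analysis plan specifies a GEE Poisson regression for rates with robust standard errors. On time it says: "To account for seasonality a harmonic term for time (in months) will be included". It names no South/North term, no group-specific time term and no calendar-period effects. It also says that "data collected during the transition period for each cluster will not contribute to the analysis". Confounders enter the main analysis there only where the allocated order is broken.

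Under Research-specific challenges and limitations, the article notes the new tank starting midway, the overlapping steps and the heterogeneity of clusters. It says: "These aspects will be accounted for in the stepped-wedge analysis by considering potential confounders". The South-first order is not among the aspects listed.

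**The concern.** In a stepped wedge, the randomised evidence is the comparison of clusters that could have exchanged places in the order. Here a South cluster could never have exchanged places with a North cluster, because funding and works planning fixed which group came first. A model with one time course for the town still uses treated South against waiting North as if the two were exchangeable.

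This matters only if the groups move differently over time, and the article gives reasons to expect that they may. The groups are defined by the tank that mainly serves them, and the new tank enters service partway through. Flooding, a vaccination campaign or a local outbreak could also hit one half of town harder. The model could then attribute such a divergence to the taps. Robust standard errors over 16 clusters do not capture it, because the shock is shared by all clusters of a group. The result would be reported as randomised evidence although part of it is not.

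**Working it through.** **1. The groups, from Table 1.** Positions 1-6 are clusters 10, 15, 14, 13, 11 and 16; positions 7-16 are the other ten.
- South: 171,741 people and 56.5 suspected cases per month, so 56.5/171.741 = 0.33 per 1000.
- North: 89,221 people and 49.1 cases per month, so 49.1/89.221 = 0.55 per 1000.

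**2. Who is compared with whom.** Let position k start in 4-week period k, with 8 weeks (periods k and k+1) excluded. In period t the treated positions are k ≤ t−2 and the waiting positions are k > t.
- Within South, both exist only for t = 3 to 5.
- Within North, both exist only for t = 9 to 15.
- In periods 6-8 the only same-period comparison is treated South against waiting North.
- In periods 3-5 and 9-15, South-versus-North comparison is mixed with within-group comparison.
- Periods 1-2 have no treated cluster and period 16 has no waiting one.
- With a 4-week exclusion, the South window is periods 2-5 and the North window is periods 8-15.

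**3. The stated minimum detectable difference.** Inputs from the Sample size section: rate p = 0.4 per 1000, 16,000 people (read as per cluster-month), ICC 0.3, 80% power, 5% level (taken as two-sided). The Hussey-Hughes variance with common period effects, I = 16 clusters, T = 17 periods, one cluster per step and nothing dropped is, for a between-cluster variance that is large against the within part:

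var = I·T·σ² / D, with D = U² + ITU − TW − IV and σ² = p(1−p)/16,000 = 2.499×10⁻⁸.

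U is the total of treated cluster-periods. W is the sum of squared period totals and V the sum of squared cluster totals.

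U = 136 and W = V = 1496, so D = 18,496 + 36,992 − 25,432 − 23,936 = 6120. The SE is √(272 × 2.499×10⁻⁸/6120) = 0.0333 per 1000, and the MDD is 2.80 × 0.0333 = 0.093. That rounds to the stated 0.1. Power at exactly 0.1 is 85%.

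**4. How much of that is randomised.** With group-by-period effects, only within-group comparison remains, and information D/(I·T) adds over the groups.
- South: U = 81, W = 451, V = 1111, D = 490; 490/102 = 4.80.
- North: U = 55, W = V = 385, D = 1980; 1980/170 = 11.65.
- Sum 16.45, against 6120/272 = 22.50 for common periods.

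The South-versus-North share is 1 − 16.45/22.50 = 27%. The SE rises by √(22.50/16.45) = 1.17, the MDD to 0.109, and power for 0.1 falls to 73%.

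Generalised least squares extends this to 0, 1 or 2 months dropped, 1-12 months before and 0-12 after roll-out, equal or Table 1 case weights, and between-cluster variance from zero to very large. With common period effects the share is:

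| Months dropped | South-versus-North share | MDD, common periods → group-by-period | Power for 0.1 per 1000 |
|---|---|---|---|
| 0 | 27-52% | 0.093 → 0.109 | 85% → 73% |
| 1 | 37-59% | 0.097 → 0.123 | 82% → 63% |
| 2 | 46-66% | 0.104 → 0.141 | 77% → 51% |

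**5. The model as written.** With one town-wide harmonic and no period effects, the information splits into three parts:
- randomised within-group comparison, 6-34%;
- South versus North in the same month, about 10-31%;
- before-after comparison, about 38-84%.

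**6. What a divergence could do (illustrations only).** Suppose the tank cut incidence 20% more in North. With cluster and common period effects, a null tap effect would then appear as a rate ratio of 0.97-1.10, depending on when the tank starts. In simulation with assumed group shocks of SD 0.2 or 0.4 on the log scale, common period effects rejected a true null in 8-15% or 20-33% of trials. Group-by-period effects rejected in about 3-4%. With no group shock, the common-period model rejected in 3.5-3.9%.

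**The case against.** **The share depends on the model.** A reader might infer that a third to two thirds of the planned evidence is South versus North. The Analysis plan does not support that: the larger shares need common calendar-period effects, which it does not state. Under its harmonic the figure is 10-31%. This stands. The randomised part is then also small, because before-after comparison supplies most of the rest.

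**Within-group comparison is available for most of the roll-out.** A reader might infer that outside two short windows everything rests on South versus North. With 8-week exclusion, that is true only of periods 6-8. A randomised contrast exists in 10 of the 13 periods that have both treated and waiting clusters, and 8 weeks is a maximum.

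**The harm is assumed.** No section gives a differential tank effect or a size for group shocks. The article expects the tank to help every cluster and lists it as part of the intervention. The simulated error rates and the tank bias were obtained with common period effects, so they are not properties of the plan. This stands.

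**The article already has safeguards.** It promises a water service indicator, attention to confounders and a separate interrupted time series. The indicator might absorb part of a tank-driven change, but its content is left open and it would not cover an outbreak or a vaccination campaign. Confounders that are constant over time cannot absorb diverging time courses. The time series is a before-after analysis and does not repair the stepped-wedge estimate. A fuller analysis plan, not shown, might add stratum-by-time terms; the published primary model does not.

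**Stratifying time costs precision.** This is correct, and it is why full group-by-period effects need not be the primary choice.

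**Conclusion.** The concern holds in limited form. Randomisation was within South and within North, the order of the groups was fixed, and the stated primary model takes no account of this. A non-randomised South-versus-North contrast therefore contributes about 10-31% of the information under the harmonic as written, or about 27-66% under common period effects. The ranges assume monthly periods, one cluster per step, a normal approximation, and a range of weights and pre/post lengths. They cannot be narrowed, because the trial diagram is not shown and the working correlation is not stated.

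The documents do not show that the estimate will be biased, in which direction, or by how much. They show that a time course differing between the groups can enter the tap effect, and that the stated standard errors would not reflect it.

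**What to change.** In the primary stepped-wedge model, for both outcomes, add a South/North term and let the harmonic, a linear trend and a new-tank step differ between the groups. Base the p-value on re-randomising the order within South and within North only. Report two sensitivity analyses: full group-by-period effects, and the single town-wide time course. Describe the South-versus-North part of the latter as non-randomised.

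This changes analysis wording and needs no new data, but it costs precision:
- Group-specific smooth terms raise the SE by about 2-35% over the same kind of time terms shared by the town.
- Full group-by-period effects raise it by about 22-62% over common period effects when one or two periods are dropped. Power for 0.1 per 1000 is then 51-73% instead of 77-85% over the three rows of the table.
- Against the harmonic alone the nominal loss is larger. For full group-by-period effects it is a factor of 1/√0.34 = 1.7 to 1/√0.06 = 4.1. For the group-specific smooth terms, the same least-squares calculation gives about 1.6-2.5. Most of the precision given up there comes from before-after comparison and South versus North, not from the randomised order.

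The Sample size section should therefore restate the minimum detectable difference for the model chosen.
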